### Participants

Twenty alcohol-dependent, 20 cocaine-dependent and 20 healthy control individuals will be recruited to take part in the study (for power calculation, please see “Statistics”). Patients from the inpatient and outpatient branches of the clinic will be informed about the study by physicians, fliers and, in the case of the inpatient clinic, periodic visits from the investigators. All individuals receiving treatment for one of the substance use disorders in question will be approached, in order to ensure that as many individuals as possible who fit the inclusion criteria are reached. The mean age and gender distribution of the cocaine-dependent and alcohol-dependent participants combined will be used as a guide for finding matched healthy controls. Alcohol-dependent and cocaine-dependent individuals will be recruited from the University Psychiatric Clinic of the University of Basel.

Inclusion criteria for these individuals are: age between 18 and 75 years; meeting three or more of the DSM-IV criteria for substance dependence (as determined by the treating physician); minimum of 20 days and maximum of 40 days abstinence from substance of dependence; able to understand and complete the informed consent; able to travel to study site independently, as confirmed by the treating psychiatrist; assessed for physical and mental fitness by the treating physician; and cleared to take part in the study.

The healthy control group will be recruited through personal contacts (the friends and family members of the investigative team and other employees of the Department for Sport, Exercise and Health) and matched for age and gender. Inclusion criteria for the healthy control group are: age between 18 and 75 years; fewer than 3 h of physical exercise or sport per week; and no history of problematic alcohol or illicit drug consumption. All participants will receive a written document outlining the requirements of the study, and informing them that withdrawal at any point will not adversely affect their medical treatment. Participants who agree with the terms will sign the adjacent consent form in the presence of a member of the investigative team, who can also answer any questions arising during the consent process.

Participants will receive a financial incentive of 150 CHF for completion of all three measurements periods, and travel costs will be refunded. Participants will continue to receive treatment as usual during the study phase. In order to optimise participant retention, participants will be contacted by telephone if any of the three scheduled sessions are missed, in order to ascertain, if possible, whether a new session can be scheduled or whether the participant wishes to cease their involvement in the study. Participants may also request telephone or text message reminders of their scheduled sessions.

Prior to the baseline session, all participants will undergo a resting echocardiogram on arrival at the test laboratory. Any participants with questionable findings will be excluded from further participation and referred to their treating physician. Further exclusion criteria include: illness during the study period; inability to complete either exercise condition; and failure to attend three sessions at a maximum of 4 days apart. Participants are not prohibited from any activities during the trial. Any adverse events occurring during the trial will be documented, submitted to the treating physician and ethical committee, and may, upon discussion with the treating physician, lead to exclusion of the participant from the trial.

Data for all participants will be stored only at the intervention site, in coded form, with the key only available to the onsite investigative team. No data from participants who do not complete the full study will be retained or analysed. A single member of the team is responsible for coding, and the code key is locked in a single office at the investigation site. Data entered electronically are not linked in any way to this code list; hard copies of questionnaires are stored in a separate archive. Data entry will be controlled by the principal investigator following entry by other investigators, comparing hard copies with electronic records. Following the trial, archived material will be kept for 10 years, in line with the requirements of the local ethics committee. An inventory of each section of the trial is visible in the SPIRIT checklist (Additional file 1).

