### Statistics

Sample size is calculated a priori using G*Power 3.1 [58]. Based on effect sizes reported in previous studies [25, 40] and an alpha level set to 0.05, the initial power analysis indicates that 17 participants per group are required to reach 85% statistical power. As drop-outs have to be expected, the sample size is increased to 20 participants per group. Note that the power analysis is based on the acute effects of moderate aerobic exercise on prefrontal cortex activity and inhibitory control. The statistical analysis of collected data is performed with SPSS 23.0 (IBM Statistics, USA) for Windows. Acute effects of exercise on inhibitory control and HbO_2_ concentration are examined using a 2 (group: alcohol dependent, healthy controls) × 3 (condition: control, moderate exercise, highly intense exercise) × 2 (time: pre, post) ANOVA on reaction time and the haemodynamic response to incompatible trials of the Stroop colour–word test. Additionally, effects of exercise on cue-elicited craving and HbO_2_ concentration (neutral cues subtracted from alcohol/cocaine cues) are investigated by applying a 2 (group) × 3 (condition) × 2 (time) ANOVA. Main effects and interactions are reported. Subsequently, Bonferroni-corrected *t* tests are used to decompose any significant interactions. The level of statistical significance is set to *p* < 0.05. Data from participants who do not complete all three measurement points will not be used.

Regarding missing data, as participants who do not complete all three sessions will be excluded from the study, it is anticipated that missing data will chiefly be due to faults in the fNIRS and Stroop programming, and thus will be missing at random. For this reason, multiple imputation will be used to address this issue.

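### Healthy controls are matched to the two patient groups combined, but the only group contrast the plan names is alcohol dependence against controls, so age and gender balance is not assured there

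*Protocol article*

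**What the plan says.** **Matching target.** Protocol article, Methods, Participants: the average age and the gender mix of the two patient groups' "participants combined will be used as a guide for finding matched healthy controls". Later in the same section the control group is described as recruited through personal contacts "and matched for age and gender", without naming the group it is matched to.

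**Group sizes.** "Twenty alcohol-dependent, 20 cocaine-dependent and 20 healthy control individuals will be recruited to take part in the study". The permitted age range is 18 to 75 years for patients and controls alike.

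**Analysis.** Methods, Statistics describes two ANOVAs, each with two groups, three conditions and two time points.
- Stroop reaction time and the haemodynamic response: the factor is given as "group: alcohol dependent, healthy controls".
- Cue-elicited craving and the haemodynamic response to cues: the effects "are investigated by applying a 2 (group) × 3 (condition) × 2 (time) ANOVA". The two levels are not named here, and the outcome refers to alcohol or cocaine cues.

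Main effects and interactions are both to be reported. Neither description mentions age or gender. The General stress section raises perceived stress as a possible covariate, and the Demographic data section records age and gender for everyone.

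**The concern.** Patients and controls are not randomised to their group. Matching is the only means the article names of keeping age and gender out of a patient-control difference. Matching to a combined target suits a comparison of all patients with controls, but the article does not state such a comparison. The contrast it does name uses one patient group, while the other supplies half of the target.

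If alcohol-dependent and cocaine-dependent participants differ in age or gender mix, a control group placed between them is displaced from both. Reaction time and haemodynamic response plausibly vary with age. Part of a reported alcohol-control difference could then be an age or gender difference.

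**Working it through.** The plan states no figure for the achieved or expected balance, so there is none to reproduce. The sample-size figure of 17 per group does not bear on this point.

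**Step 1. Displacement of the controls.** Let A and C be the mean ages of the alcohol and cocaine groups, with sizes nA and nC. Controls who meet the target have mean (nA·A + nC·C)/(nA + nC). Their distance from the alcohol group is

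control mean − A = nC/(nA + nC) × (C − A).

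With nA = nC = 20 (Participants) the factor is 20/40 = 0.5. It depends on who is recruited and retained: 20/37 = 0.54 with 17 alcohol and 20 cocaine patients, and 8/28 = 0.29 with 20 and 8.

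**Step 2. Size for assumed gaps.** The article gives no ages, so the gap and an age SD of 10 years are assumptions.

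| Assumed alcohol-cocaine age gap (years) | Controls vs alcohol group (years) | In SD units |
|---|---|---|
| 0 | 0 | 0 |
| 5 | 2.5 | 0.25 |
| 10 | 5 | 0.50 |
| 15 | 7.5 | 0.75 |
| 20 | 10 | 1.00 |

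The same rule applies to gender. Assumed male shares of 60% and 80% give a combined share of 70%, which is 10 percentage points from the alcohol group. Shares of 50% and 90% give 20 points, and equal shares give 0.

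**Step 3. Effect on a group main effect.** Assume a slope of 0.3 to 0.5 outcome SD per age SD. The spurious difference is d = imbalance × slope. For a two-sided 5% test with 20 per group, the false-positive rate comes from a noncentral t distribution with 38 degrees of freedom and noncentrality d × √(20/2).

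| Imbalance (SD) | Slope 0.3: d, false-positive rate | Slope 0.5: d, false-positive rate |
|---|---|---|
| 0.25 | 0.08, 5.6% | 0.13, 6.7% |
| 0.50 | 0.15, 7.5% | 0.25, 12.0% |
| 0.75 | 0.23, 10.7% | 0.38, 21.2% |
| 1.00 | 0.30, 15.2% | 0.50, 33.8% |

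At zero imbalance the rate stays at 5%.

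**Step 4. Which effects are touched.** Write a participant's outcome as group effect + β × age + condition and time effects + error.
- *Group main effect:* it carries β × (difference in mean age).
- *Within-person contrasts:* post minus pre, and exercise minus rest, are taken in the same person, so β × age cancels.
- *Group × condition × time:* β × age cancels here too. An age difference enters only if the slope on age itself changes with condition and time, that is, if age modifies the response to exercise. The same holds for gender.

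**The case against.** The strongest reply is that this reaches little of what the trial sets out to test. The hypotheses at the end of the Background compare exercise with the passive condition within dependent participants. The one expectation for controls, no altered cue response after any condition, is also within-person. This stands, and it limits the point to between-group effects. Exercise intensity is also set relative to an age-estimated maximal heart rate, which makes modification by age less likely without excluding it.

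Second, a reader might infer that the controls are in fact not matched. The documents do not support that. Imbalance needs a difference between the patient groups, and none is reported.

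Third, a reader might infer that the article contradicts itself or claims to have removed age and gender differences. It does neither. It discloses the combined target, calls it a guide, and never says that controls match the alcohol group alone.

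Fourth, only the Stroop ANOVA names its groups. If the cue-craving ANOVA compares all patients with controls, the combined target is appropriate for it. One control group of 20 serving two patient groups also makes the combined target a reasonable compromise. Both points stand.

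Fifth, covariates may be settled in an analysis plan that is not shown. Their absence is therefore not the point. The point is that the stated matching target and the stated contrast do not fit each other. Nor is it worth pressing that a matched mean leaves the age spread open, since the target is only a guide.

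**Conclusion.** The point holds in a limited form: the matching rule does not assure age and gender balance for the one group contrast the article names. The displacement is half of any difference between the patient groups at 20 and 20, ranging from zero to 10 years for assumed age gaps of 0 to 20 years. For an assumed 10-year gap, an age SD of 10 and a slope of 0.3 to 0.5, the false-positive rate of an unadjusted group main effect would be about 7.5% to 12% instead of 5%. The gap, SD and slope are all assumptions.

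The bias concerns group main effects. It concerns group interactions only if age or gender modifies the exercise response. It would be wrong to read it as a threat to the within-patient comparisons of exercise with rest.

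**What to change.** 1. State for each ANOVA which patient group or groups are compared with controls, including whether and how the cocaine group is compared with them.
2. Include age (mean-centred) and gender as covariates in every comparison with a group factor. Centring matters because an uncentred covariate in a repeated-measures model changes what the condition and time main effects test.

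No new data are needed. In a comparison of 20 with 20, the between-participant error degrees of freedom fall from 40 − 2 = 38 to 38 − 2 = 36. If the covariates are also crossed with the within-person factors, the condition × time error falls from 2 × 38 = 76 to 2 × 36 = 72.

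Rematching controls separately to each patient group is not recommended. The same 20 controls serve both, so moving them towards one group moves them away from the other whenever the two differ.

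### Completers-only rule, applied after the session order is allocated, discards valid sessions and limits every contrast to people who managed both exercise bouts

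*Protocol article*

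**What the plan says.** The rule appears twice. In Participants: "No data from participants who do not complete the full study will be retained or analysed". In Statistics: "Data from participants who do not complete all three measurement points will not be used".

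Participants lists what leads to exclusion once someone is in the study: "illness during the study period; inability to complete either exercise condition; and failure to attend three sessions at a maximum of 4 days apart". An adverse event may also end participation, after discussion with the treating physician. A missed session is not an immediate exclusion: the team telephones to find out "whether a new session can be scheduled or whether the participant wishes to cease their involvement in the study".

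On missing data, Statistics reasons that, with non-completers already out, "it is anticipated that missing data will chiefly be due to faults in the fNIRS and Stroop programming, and thus will be missing at random", and concludes that "multiple imputation will be used to address this issue".

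On safety, Participants says: "Any adverse events occurring during the trial will be documented, submitted to the treating physician and ethical committee". That sentence is not limited to completers.

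**The concern.** Under Study design, the order envelopes are handed out at recruitment, so all of these exclusions come after randomisation. At least one, "inability to complete either exercise condition", is tied to the intervention itself. Because failing either bout removes the whole person, someone who cannot finish the intense session also disappears from moderate exercise versus rest, although those two sessions may be complete and valid.

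The trial's stated interest is in integrating exercise into treatment. Who can manage the bouts is part of that question, and the plan leaves those who cannot out of the answer. Losses to equipment faults are imputed, while losses that could be related to the conditions are deleted.

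Non-retention is more serious than the choice of analysis set. A narrow analysis set can be supplemented later, but data that were not kept cannot be recovered by any later analysis plan.

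**Working it through.** **1. Order of events.** Recruitment, then allocation of order (Study design), then three sessions 2 to 4 days apart (Experimental conditions), with exclusions acting along the way (Participants). A participant who fails the intense bout in the third session loses two completed sessions.

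**2. The plan's own allowance.** Statistics gives 17 per group for 85% power at alpha 0.05, raised to 20 for drop-outs. No rate is stated. The implied rate is 1 − 17/20 = 0.15, and 17/(1 − 0.15) = 20 confirms the step. The 17 itself cannot be reproduced, because no effect size, correlation or test is given.

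**3. Chance of keeping at least 17 of 20** (binomial, independent losses; rates assumed):

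| Non-completion | P(at least 17 complete) |
|---|---|
| 10% | 0.87 |
| 15% | 0.65 |
| 20% | 0.41 |
| 25% | 0.23 |

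If 17 came from a two-sided paired t test (an assumption; it implies d = 0.77), power would be 80% with 15 completers and 76% with 14. This concerns precision only. Recruiting more people does not remove selection.

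**4. How far the completer mean could move.** Suppose a tolerance trait and the individual effect are bivariate normal with correlation r, and the lowest fraction q on tolerance do not complete. The completer mean then differs from the all-randomised mean by

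shift = r × φ(z_q) / (1 − q), in SDs of the individual effect.

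For q = 0.15 the multiplier φ(z_q)/(1 − q) is 0.274, so r = 0.5 gives 0.5 × 0.274 = 0.14.

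| q | r = 0 | r = 0.3 | r = 0.5 |
|---|---|---|---|
| 10% | 0 | 0.06 | 0.10 |
| 15% | 0 | 0.08 | 0.14 |
| 25% | 0 | 0.13 | 0.21 |

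Neither q nor r is in the document. The sign of r is also unknown, so the shift could go either way. For scale, the standard error of a paired contrast with 17 completers is 1/√17 = 0.24 SD of the paired difference, so the illustrated shifts are smaller than one standard error.

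**5. Between-group tests and order balance.** The planned ANOVA crosses group, condition and time. Non-completion may differ between patients and healthy controls, and then the groups compared are selected to different degrees. Deleting whole participants can also unbalance the randomised orders, and the ANOVA has no term for session order.

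**6. Safety text side by side.** One sentence in Participants requires any adverse event to be documented and sent to the treating physician and ethics committee, and foresees that an event may lead to exclusion. The next paragraph keeps no data from anyone who does not finish. The article does not say which governs the trial's own records for someone excluded because of an event.

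**The case against.** Each participant is their own control, so contrasts among completers remain within-person comparisons, and the main consequence is a narrower target population. That stands for the condition contrasts within a group. It does not protect the group-by-condition-by-time tests.

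Physician clearance, cardiac screening before baseline, reminders, rescheduling and payment for completion should keep losses low. These are real safeguards, but the plan itself expects drop-outs.

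Four stronger readings are tempting, and the document does not support them:

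- That anyone who misses a session is out. A new session may be arranged; exclusion follows only if three sessions within the spacing limit are not achieved.
- That harms in non-completers are lost. The adverse-event duty covers them. What remains is the unreconciled conflict in step 6.
- That relapse removes a participant. Abstinence of 20 to 40 days is an entry criterion, and relapse is not among the listed exclusions.
- That deletion favours a craving benefit. The direction is unknown. For intense exercise the stated hypothesis is no effect on craving, so a shift towards benefit would count against it.

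A mixed model is also no complete cure. It relies on missing at random, and if completion depends on the unobserved response to the bout, bias remains. Its certain gain is recovering sessions that were completed. Multiple imputation for technical faults is a reasonable method, and replacing it would be a matter of preference.

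**Conclusion.** The concern holds in this form. The plan explicitly excludes participants after allocation, for reasons that include failing an exercise bout, and neither keeps nor analyses their data. All contrasts then describe people who could complete both bouts, valid sessions are wasted, group comparisons may rest on differently selected groups, and order balance may be lost.

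No definite bias can be claimed. The range of 0.06 to 0.21 SD of the individual effect rests on assumed non-completion of 10 to 25% and an assumed correlation of 0.3 to 0.5. It falls to zero if completion is unrelated to effect. On safety, the supportable statement is that non-completers' events and stopping reasons could drop out of the trial dataset and report, because two statements in Participants are not reconciled.

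**What to change.** - Delete the completers-only rule in both Participants and Statistics. This changes data handling only, not who stops taking part.
- Retain all data collected up to withdrawal, as consent allows.
- Analyse all available sessions of every randomised participant with a likelihood-based linear mixed model: condition, time, group and their interactions, session number, and a random participant effect. State that it relies on missing at random.
- Keep the completers analysis as a sensitivity analysis. Multiple imputation for fNIRS and Stroop faults may stay.
- Report non-completion with reasons, and adverse events, by condition for everyone who started a session.
- Reconcile the adverse-event sentence with the no-retention sentence in Participants.

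The cost is protocol wording, an ethics and consent notification, and slightly more analysis work. No additional participants are needed. The consent text is not available here, so whether data from anyone who has already withdrawn may be kept has to be checked locally. The article gives recruitment as incomplete, so the retention rule should be changed first.

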### Timeline of assessments

Figure 1 demonstrates the proposed schedule of assessments for each individual participant.

**Fig. 1 Fig1:**
[figure not shown]
Schedule for each participant in each condition. fNIRS functional near-infrared spectroscopy, HbO_2_ oxygenated haemoglobin, HRM maximal heart rate, PSS Perceived Stress Scale

Figure 2 shows the SPIRIT figure for a single participant in the study.

**Fig. 2 Fig2:**
[figure not shown]
Example of timeline of assessments for a single participant

### Measures

#### Demographic data

The age and gender of all participants will be recorded. Alcohol-dependent and cocaine-dependent participants will be asked to report the year of onset of their dependence, the number of treatment attempts made to date, the number of days of the current treatment episode, the number of days of abstinence and their nicotine consumption.

#### General physical exercise and activity

The SIMPAQ is a brief five-item tool, which comprehensively evaluates activity over the past 7 days including time in bed, sedentary time, time spent walking, type of and time spent in exercise, and time spent for other activities [42]. Assessed physical activity refers to all domains of activity, including leisure time, domestic, work and transport-related activities. The SIMPAQ captures a 24-h period representative for the previous week.

It is important to assess the physical activity levels of participants, as more active individuals may not experience clear changes in prefrontal activation following an acute exercise bout.

